##### Secondary (exploratory) endpoints and control variables

Depending on the scales, the secondary endpoints will be reported descriptively as means with standard deviations, medians, and frequencies. If tests will be conducted, then an alpha less than 0.05 is considered as significant. All these tests are exploratory to get additional ideas on the impact of the treatment.

### Definition of collective analysis

All patients who fulfill the determined inclusion criteria will be used for the data analysis, independent of whether the intended shock wave therapy is performed as planned (intention-to-treat analysis).

### Handling of missing, unused, or faulty data; drop-outs; and terminations

In order to counteract missing values as best as possible, the study will be carried out according to the GCP principle (Good Clinical Practice). Additionally, a regular evaluation of the collected data will take place. If missing values are detected, an attempt will be made to subsequently determine them and/or to document the reasons.

Missing values concerning the primary endpoint are estimated according to the Last Observation Carry Forward principle (LOCF). If possible, the same procedure is used for the secondary endpoints. In all other cases, an analysis of the observed data will be carried out.

The systematically documented reasons for drop-outs will be evaluated to see if they can be used as a predictor for the endpoints and thereby additional insights into the therapy can be gained.

A sensitivity analysis will be performed in order to estimate the effect of missing data and outliers on the study endpoints.

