Improvements in diagnostics, pre-hospital management, fast transfer to specialized units, good shock management, the potential for early surgical decompression, and advanced medical rehabilitation methods result in higher life expectancy and lower mortality rates in high-income countries [5, 9]. Though, life expectancy after SCI is reduced compared to the general population. The mortality depends on the level and severity of the lesion and the availability of clinical care. Mortality is particularly high in the first year after injury [5].

Despite worldwide intensive efforts, SCI remains a devastating condition for which there is yet no causal treatment available [10].

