### Extracorporeal shockwave therapy (ESWT) in patients with chronic complete paraplegia (AIS A) at the thoracic level

In 2015, recruitment for a multi-center prospective randomized double-blind clinical study was started including patients suffering from chronic paraplegia (lesion between THII and THX, AIS A = complete central lesion) at least for 1 year after the initial trauma without spontaneous recovery within the last 6 months. In general, a spontaneous recovery of the senso-motoric function is decreasing with the time from injury and is therefore not expected in the study population. In these cases, treatment options are mainly limited to the improvement of the quality of life.

Currently, 34 patients from the intended 50 have been included in the study and recruitment is ongoing until the end of 2020. Therefore, results are not available yet. Until now, no severe side effect or adverse effect occurred to the study participants. Besides the multi-parametric evaluation (neurological, neurophysiological, clinical as well as functional), blood samples have been collected to multiplex protein assessment miRNA analysis.

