### Study endpoints

#### Primary endpoint

It is assumed that patients who suffer acute SCI regain more of their motor and sensory functions because of treatment with EWST than patients in the control group. Six months after the baseline measurement, patients will be invited for a follow-up visit as soon as possible. The primary endpoint will be a composite endpoint composed of the ISNCSCI subscores — motor and sensory function — to achieve the required power of the study with the expected incidence. These subscores and all secondary endpoints will be analyzed descriptively to provide further insight or to derive hypotheses as appropriate.

The primary composite endpoint is calculated as the difference between the upper and lower extremities motor score (ULMS + LLMS), light touch (LT), and pin prick (PP) at two points in time.

delta.TMSC = TMSC_after 6 months_ minus TMSC_at baseline_

TMSC = Total motor and sensory score

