### Study procedures

First, eligibility for study participation will be assessed and informed consent will be obtained in a pre-screening. Additionally, a pregnancy test will be performed in women with childbearing potential prior to the study intervention. After that, eligible patients undergo a baseline examination comprising a short medical history, a neurological examination (AIS/ISNCSCI), radiological imaging, assessment of the presence of pathological reflexes (priapism, plantar reflex), and documentation of pre-operative interventions.

ESWT is applied peri-operatively under general anesthesia (ideally post-operative immediately after skin closure) or within the first 48 h after trauma.

After the study intervention, surgical interventions and intra-operative diagnosis shall be documented. Also, findings from post-operative imaging and the time sequence of the acute care chain are recorded.

The first follow-up exam should be performed as early as 24–72 h after surgery consisting of a comprehensive medical history and drug anamnesis, an assessment of pre-existing neurological deficits, a neurological examination (AIS/ISNCSCI and plantar reflex), a gait analysis, assessment of urological function, rating of injury severity (Injury Severity Score (ISS)), survey of comorbidities (Charlson Comorbidity Index (CCI)), and questionnaires addressing activities of daily life (Spinal Cord Independence Measure (SCIM) and the Walking Index for Spinal Cord Injury II (WISCI II)). Also, a patient diary is handed out to every patient during the first study visit in which patients should record spasms (Penn Spasm Frequency Scale), medication (drug name and dosage), and any important subjective or objective changes in the neurological symptoms.

The 2nd (day 14–21), 3rd (3 months), and 4th (6 months) follow-up visits consist of a neurological examination, a gait analysis, assessment of urological function, and questionnaires addressing activities of daily life. Parameters from routine blood chemistry and changes in medication shall be documented at each study visit. At the last follow-up exam (6 months), the stability of osteosynthesis is re-evaluated according to X-ray/CT, and a copy of the patient diary is filed at the study site.

The study procedures are depicted in a flowchart, as well as in tabular format in the supplementary material.

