#### Data analysis

##### Calculation of the composite endpoint

In general, following the intention-to-treat (ITT) approach, all patients are included in the analysis. For scale variables, the means, standard deviations (SD), median values, and minimum/maximum values will be given. For ordinal variables, medians and minimum/maximum values will be calculated and reported. Frequencies and percentages will be given for nominal variables. Missing values are not considered when calculating the percentage.

The International Standards for the Neurological Classification of Spinal Cord Injuries (ISNCSCI) was chosen as the relevant clinical endpoint for this study. This score includes several subscores, which are listed in the table below.

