**Composite Endpoint: delta.TMSC = TMSC after 6 month - TMSC at baseline**

The entire measuring process is illustrated in the following figure.

[figure not shown]

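### LOCF as the primary missing-data rule understates a 6-month change that the trial expects to keep rising, and biases the comparison if loss or its timing differs between arms

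*Protocol article*

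**What the plan says.** The section on handling of missing data and drop-outs fixes the rule: "Missing values concerning the primary endpoint are estimated according to the Last Observation Carry Forward principle (LOCF". It names no exception. The endpoint is "delta.TMSC = TMSC after 6 month - TMSC at baseline".

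The values that could be carried forward come from the schedule in Study procedures. "The first follow-up exam should be performed as early as 24–72 h after surgery", and then "The 2nd (day 14–21), 3rd (3 months), and 4th (6 months) follow-up visits consist of a neurological examination". Apart from baseline, the scores available before the endpoint visit are thus those at 24–72 h, day 14–21 and 3 months.

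The analysis set is everyone: "following the intention-to-treat (ITT) approach, all patients are included in the analysis". The Primary endpoint section assumes that "patients who suffer acute SCI regain more of their motor and sensory functions because of treatment with EWST than patients in the control group", and the section on hypothesis formulation says that improvement over time is what the trial looks for. A sensitivity analysis for missing data and outliers is promised in two places. The article does not describe its method, and it does not displace LOCF as the primary rule.

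**The concern.** LOCF gives the right 6-month value only if the score stays flat after the last visit. This trial is built on the opposite expectation: function returns over the 6 months, and more of it with treatment. A score taken days or weeks after injury then stands in for a 6-month result and omits whatever recovery, and whatever treatment effect, comes later.

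Two things follow. Where loss is the same in both arms, the difference between arms is pulled towards zero. Where loss, or its timing, differs, the arm that loses more patients or loses them earlier looks worse for that reason alone. If that is the control arm, the one-sided test favours treatment. The same imputed values would enter the two interim looks, and a wrong stop for success or for lack of efficacy cannot be repaired by a later sensitivity analysis.

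**Working it through.** **Inputs from the article.** One-sided alpha 5%, power 80%, probability of a better result 0.6 against 0.5, 1:1 allocation, 41 per arm per stage, upper bounds 2.13, 1.89, 1.85 and lower bounds 0.00, 1.13, 1.85, maximum 246.

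**Reproducing the design.** The standardised effect is d = √2 × z(0.6) = 1.414 × 0.2533 = 0.358 SD. With the stated bounds and correlation √(i/j) between looks, alpha is 0.0497 and power is 0.807 at 41 per arm per stage (0.799 at 40). So 41 is the smallest stage size that reaches 80%, and 6 × 41 = 246 is reproduced. The design is sound on its own inputs.

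**Assumptions, none of them in the article.** SD of delta.TMSC = 1; loss of 10–20%; mean 6-month recovery μ in the control arm of 0.5, 1.0 or 1.5 SD; a fraction f of the 6-month change visible at the last observed visit. Where loss is spread evenly over visits, f is 0, 0.1, 0.3 and 0.7 at baseline, 24–72 h, day 14–21 and 3 months, a mean of (0 + 0.1 + 0.3 + 0.7)/4 = 0.275. The simulations use 20,000 trials per line; repeat runs agree to about 0.01.

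**Equal loss q, equal timing.** Estimated effect = d × (1 − q(1 − f)). At q = 0.20 and μ = 1 SD:

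| f at last visit | effect retained | LOCF power (simulated) |
|---|---|---|
| 0 | 80% | 0.63 |
| 0.3 | 86% | 0.72 |
| 0.5 | 90% | 0.77 |
| 0.7 | 94% | 0.79 |

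Holding the SD at 1 instead gives 0.64, 0.70 and 0.76 for f = 0, 0.3 and 0.7. The fair reference is not 0.81, which no method restores once patients are lost. It is an unbiased analysis of 41 × 0.8 = 32.8 patients per arm per stage, with power 0.73. LOCF falls clearly below that only when f is less than about 0.3. Type I error stays at about 0.05 throughout.

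**Unequal loss, spread over visits, no true effect.** Bias = (loss in control − loss in treatment) × (1 − 0.275) × μ. With 10% lost on treatment and 20% on control and μ = 1, this is 0.10 × 0.725 × 1 = 0.0725 SD, or 0.0725/0.358 = 20% of the planned effect.

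| μ (SD) | bias (SD) | one-sided type I error, 10% vs 20% | power when reversed, 20% vs 10% |
|---|---|---|---|
| 0.5 | 0.036 | 0.08 | 0.63 |
| 1.0 | 0.073 | 0.13 | 0.50 |
| 1.5 | 0.109 | 0.18 | 0.38 |

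If loss were spread over the three post-baseline visits only, mean f = (0.1 + 0.3 + 0.7)/3 = 0.367 and the bias at μ = 1 is 0.10 × 0.633 = 0.063 SD. The mechanism does not depend on carrying baseline forward.

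**Equal 15% loss, earlier in controls.** With weights over the four occasions of 0.1, 0.1, 0.2, 0.6 on treatment (mean f = 0.49) and 0.4, 0.3, 0.2, 0.1 on control (mean f = 0.16), the bias is 0.15 × 0.33 × μ = 0.0495 SD at μ = 1. Type I error is 0.07, 0.10 and 0.13 for μ = 0.5, 1.0 and 1.5.

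**The case against.** The other side has several good points.

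- **Unequal loss is not predicted by anything in the article.** Treatment is a single application, the control uses a dummy applicator, and patients and assessors are blinded. All type I error inflation rests on assumed imbalance. This stands, and is why the figures are illustrative.
- **The worst figures are an extreme.** Type I error of about 17% and power of about 35% arise only if every lost patient is frozen at baseline. A reader might infer that such a patient scores a change of zero, but the article does not say that baseline may be carried forward.
- **Power loss should not all be charged to LOCF.** Comparing 0.63 with 0.81 mixes the cost of losing patients with the cost of the method.
- **No acute recovery curve is given.** The remark that "a spontaneous recovery of the senso-motoric function is decreasing with the time from injury" explains why little recovery is expected in a separate trial of chronic injury. It cannot be read as a curve for this population, and if recovery were mostly early, later carried values would already contain much of it.
- **Deaths.** A reader might combine "Mortality is particularly high in the first year after injury" with LOCF and infer that the plan scores deaths as 6-month survivors. The missing-data section does not mention deaths, the sentence is general epidemiology, enrolment requires awake and oriented patients, and such detail is commonly left to the analysis plan. Its absence is no finding.
- **A sensitivity analysis is planned.** That softens the matter but leaves LOCF as the primary estimate, and nothing says that it informs the stopping decisions.

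What remains is that the article positively fixes LOCF for the confirmatory endpoint, where the score is expected to move after the last visit.

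**Conclusion.** The point holds in limited form. LOCF conflicts with the trial's own expectation that the score rises to 6 months. With equal loss and timing the test remains valid at about 5%, the effect is understated (to 80–94% of its true value at an assumed 20% loss with f from 0 to 0.7), and power is worse than that of an unbiased analysis only for early loss. With unequal loss or timing the comparison is biased in either direction: for a 10-point difference spread over visits, type I error is about 13% (8–18%), or power is about 50% (63–38%) in the reverse case, for mean recovery of 1 SD (0.5–1.5 SD).

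It would go too far to say that the result is biased whenever patients are lost. If nothing changes after the last visit there is no harm, and values from 3 months do less damage than those from the first weeks. The article gives no drop-out rate, SD or recovery curve, so the direction of the dilution is secure but the sizes are not.

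**What to change.** Replace LOCF in the primary analysis, at both interims and at the end, by one of two methods:

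- a likelihood-based repeated-measures model; or
- multiple imputation by arm, which would leave the planned block ANOVA in place.

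Either should use baseline, the ISNCSCI scores at 24–72 h, day 14–21 and 3 months, and neurological level of injury. Both assume that loss is explained by the observed data, so make a delta-adjusted or reference-based analysis part of the sensitivity analysis already promised. Keep LOCF only as a further sensitivity analysis. Add one sentence saying that patients who die are not carried forward as if they were 6-month survivors.

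The change should be settled before the first interim, because the imputed values enter that decision. It costs protocol and analysis-plan wording and modest programming, with no new visits, data or patients.

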## Discussion

Despite extensive efforts in the treatment of SCI, there is yet no causal, curative treatment approach available [10]. The current standard therapy in Austria is the early surgical decompression and stabilization [9, 11, 68] and in some cases the additional administration of steroids (methylprednisolone) in the acute phase of the injury (in the first 24–48 h, the latter being controversial) [10, 36–39].

ESWT is already being used in clinical practice such as chronic wounds, non-healing fractures, tendinopathies, myocardial ischemia, and lithotripsy. The application after acute spinal cord injury would thus be an expansion of indication for this therapy method, which has already been used in Austria for several years [12, 17, 19, 33, 34, 69].

ESWT could provide an easy-to-use, risk-free therapeutic method in the treatment of acute SCI in addition to surgical decompression with the aim of optimizing the clinical outcome.

The underlying study aims to investigate the effect of ESWT after acute traumatic spinal cord injury in humans within 48 h of trauma in order to intervene in the secondary injury phase with the objective to reduce the extent of neuronal damage.

## Trial status

Recruitment of study participants started in November 2020. Since then, recruitment takes place on an ongoing basis by admission of patients with acute spinal cord injuries. For patients who are included in the study, the follow-up phase after the baseline assessment will take approximately 6 months.

A planned interim analysis will be carried out after 41 patients have been included in each of both groups and all follow-up examinations have been completed. A further interim analysis will be planned after 82 patients per group. With unexpected major effects, the study will be prematurely terminated or, with low chances of success, will be canceled. An unplanned interim analysis will take place, should adverse events or side effects occur.

## Data Availability

Data can be made available upon reasonable request to the senior author after study closure.

## Abbreviations

AIS: American Spinal Injury Association (ASIA) Impairment Scale
AUVA: Allgemeine Unfallversicherungsanstalt
CCI: Charlson Comorbidity Index
CT: Computed tomography
DSMB: Data Safety Monitoring Board (Datensicherheitskomitee)
eCRF: Electronic case report form
ESWT: Extracorporeal shockwave therapy (extrakorporale Stoßwellentherapie)
GCP: Good Clinical Practice
GCS: Glasgow Coma Scale
GRT: Grasp and Release Test
ISNCSCI: International Standards for Neurological Classification of Spinal Cord Injury
ISS: Injury Severity Score
LEMS: Lower Extremity Motor Score
LEL: Lower extremity left
LER: Lower extremity right
LTL: Light touch left
LTR: Light touch right
LOCF: Last Observation Carry Forward principle
MAS: Modified Ashworth Scale
MF: Motor function
MPG: Medical device law (Medizinproduktegesetz)
na: Not applicable
NCI: National Cancer Institute
nd: Not done
NHPT: Nine-Hole Peg Test
NRS: Numeric Rating Scale
PSFS: Penn Spasm Frequency Scale
PI: Principal investigator
PPL: Pin prick left
PPR: Pin prick right
SAP: Statistical Analysis Plan
SCI: Spinal cord injury
SCIM: Spinal cord independence measure
SF: Sensory function
SPSS: Statistical Package for Social Sciences
TMSC: Total Motor and Sensory Score
TUG: Timed Up and Go Test
UEMS: Upper Extremity Motor Score
UEL: Upper extremity left
UER: Upper extremity right
WISCI II: Walking Index for Spinal Cord Injury II
